### Stakeholder experiences

In the three study groups, we will use PROMs to map the effectiveness and impact of RM, as estimated by the pregnant woman. The PROMs listed in Table 2 will be included in this study. Each of the PROMs will be measured using a validated questionnaire. Additionally, as PROMs recommended by ICHOM, the investigators will include EQ-5D-5L questionnaires.

**Table 2 Tab2:** Overview of patient-reported outcomes

PROM	Questionnaire
Quality of Life	EuroQoL EQ-5D-5L
Mental Health	ICHOM (Patient Health Questionnaire 2)
Satisfaction with care	ICHOM
Healthcare responsiveness	ICHOM
Birth experience	ICHOM (Birth Satisfaction Scale – Revised)

The questionnaires listed in Table 2 will be collected via a single questionnaire that will take up to 10 min to complete.

## Status of the study

Recruitment started on September 1, 2019, and enrollment will continue until September 1, 2022. After this time, follow-up will continue for 6 months. The study is at this moment ongoing, patient recruitment is not yet completed at the moment of submission of this manuscript. No other publications containing the results of this study have already published or submitted to any other journal.

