### Study design

PREMOM II is a multicenter, randomized controlled trial that will be performed at five hospitals with their own prenatal wards between October 1, 2018 and March 30, 2022. The centers combined will perform more than 7000 deliveries per year. Eligible participants will be pregnant women ≥18 years old, who are able to understand oral and written information, with a minimum risk of 1/100 on the Fetal Medicine Foundation Tool (FMF) [28, 29]. By using the FMF tool will a risk assessment for the development of early PE be made, in which the following parameters are taken into account: (1) maternal characteristics; (2) medical history; (3) obstetric history; (4) information about the current pregnancy; (5) biophysical measurements. Women will be excluded if a congenital malformation is detected or if they do not have a smartphone.

The ethics committee at Universitair Ziekenhuis Antwerpen (UZA; Wilrijk) approved the study in July 2019 (Belgium Registration Number: BE300201938651). The local ethics committees at ZOL, Universiteit Ziekenhuis Leuven (Leuven), AZ Sint Jan (Bruges), and AZ Sint Lucas (Bruges) provided advice to the ethics committee at UZA before the study was approved.

General information about the study will be available at the antenatal care units at each site. All women who are pregnant for the first time, or who had a history of GHD in previous pregnancies, are given oral and written information about the study when they undergo their first trimester ultrasound examination. They will also be asked whether they want to be screened for the development of early PE. Women who are interested in participating the study are asked to give their informed consent and their risk will be calculated using the FMF tool. Pregnant women with a risk < 1/100 will not be randomized in the study, but will receive the standard follow-up in accordance with the local routine care. Pregnant women with a risk ≥1/100 will be randomized in one of the three study groups.

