### Randomization

Figures 2 and 3 show the randomization process, trial flow and timeline table (according to SPIRIT). Randomization will be performed between 11 and 14 weeks of gestation, after the first trimester ultrasound examination. Using the Castor EDC web-based system, the women will be randomized to one of the three study groups at a 1:1:1 ratio by the study midwives, who also perform the inclusion in the PREMOM II study and the further RM follow-up (Figs. 2 and 3).

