### Data collection

Data on background variables, obstetric outcomes, and neonatal outcomes after delivery will be collected from the electronic patient files recorded at each hospital. Data on blood pressure and the associated compliance rate will be collected from DHARMA, an online platform developed by the Mobile Health Unit (Limburg Clinical Research Center, Hasselt University – ZOL - Jessa). Information about healthcare costs of pre-, peri-, and postnatal care will be collected from the Intermutualistisch Agentschap (IMA) health insurance database [41]. Information about the PROMs will be recorded using validated questionnaires.

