Based on the numbers from Studiecentrum voor Perinatale Epidemiologie (Brussels, Belgium), these 168 births before 34 weeks account for 6.6% of a total of 2545 GHD deliveries. Furthermore, GHD pregnancies represent 4.6% of the total number of pregnancies (55,335) per year [1]. As observed in prior studies, 68% of women with GHD require interventions for their GHD, we estimate a ratio of 100 to 68 pregnant women (or 1.47 to 1) will be needed for the RM group to treat one patient with GHD. As such, 6.76% (4.6% × 1.47) of these women are at risk of developing GHD, meaning 3741 women will need to be enrolled in our study. Taking into account a dropout rate of 4.83% (based on our previous studies), we will need to enroll a total of 3922 women and screen 57,998 women.

For the second sample size calculation (admission to a prenatal ward after 34 weeks), we estimated that > 360 women delivering at a gestational age later than 34 weeks will need to be enrolled across the four prenatal wards. Based on prior studies, ≥42% of women with GHD will be admitted to a prenatal ward. Therefore, out of 5931 deliveries after 34 weeks (6107 eligible women – 176 [168 + dropout rate of 4.83%] who will deliver before 34 weeks), approximately 2491 mothers will be hospitalized. As such, the sample size needed to assess this outcome is expected to be satisfied by the sample size required to show a difference in gestational age in deliveries before 34 weeks.

The primary statistical analysis will entail comparisons among the three study groups using the two-sided Fisher’s exact test at a significance level of 0.05. Adjustment for baseline variables will be performed if necessary, and interaction analyses will be performed using multivariable logistic regression analyses. The median, 95% confidence intervals, quartiles, means, and standard deviation will be calculated as appropriate.

The statistician will be blinded to the study groups.

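### Six months of follow-up after the last enrolment ends before some of the last-randomised women will have delivered, and the two stated study calendars contradict each other

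*Protocol article*

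**What the plan says.** Status of the study gives the recruitment calendar: "Recruitment started on September 1, 2019, and enrollment will continue until September 1, 2022". It continues: "After this time, follow-up will continue for 6 months". Under Randomization, entry is early in pregnancy: "Randomization will be performed between 11 and 14 weeks of gestation".

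The outcomes run to birth and beyond. Primary outcome measures include mode and date of delivery, gestational age at delivery, NICU admission and length of stay. They also include remote monitoring (RM) data, such as duration of participation and contacts, and compliance in the RM and self-monitoring groups. Data collection takes obstetric and neonatal outcomes from hospital electronic files after delivery. From the insurance database it plans "Information about healthcare costs of pre-, peri-, and postnatal care". Table 2 lists a birth-satisfaction scale.

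Study design gives a different calendar, with the trial performed "between October 1, 2018 and March 30, 2022".

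**The concern.** A pregnancy entered at 11 weeks needs 29 more weeks to reach 40 weeks, and six months supplies about 26. A fixed calendar window therefore stops before birth for some of the last women randomised, although birth and what follows it are what the trial measures. The women left out are those who deliver later, so the missingness depends on gestational age at delivery, which is itself listed as a primary outcome.

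Some of this information can be recovered from records. Some has to be gathered as it happens: home measurements and compliance up to delivery, midwife contacts, and a questionnaire about the birth. The RM group is described as the same as in the preceding study, where women recorded until delivery or hospital admission. A six-month window cannot meet that description for every late recruit.

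The second calendar adds a plain contradiction: a study period cannot end before its own enrolment does.

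**Working it through.** **Inputs from the Protocol article**
- Enrolment 1 September 2019 to 1 September 2022: 1096 days (Status of the study).
- Follow-up of 6 months after that, to 1 March 2023: 181 days, or 181/7 = 25.9 weeks (same section).
- Randomisation at 11 to 14 weeks (Randomization).
- Total enrolment 3922 (Sample size calculations). The article's chain reproduces it: 168/0.066 = 2545; 2545 × 1.47 = 3741; 3741 × 1.0483 = 3922. The figure is used here only for scale. The six months itself has no derivation to reproduce.

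**Step 1. Gestational age at closure for a woman randomised on the last day**
- Entry at 11 weeks: 11 + 25.9 = 36.9 weeks.
- Entry at 14 weeks: 14 + 25.9 = 39.9 weeks.

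**Step 2. Shortfall in days** = 7 × (target week − entry week) − 181

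| Entry | To 40 weeks | To 42 weeks |
|---|---|---|
| 11 weeks | 203 − 181 = 22 | 217 − 181 = 36 |
| 14 weeks | 182 − 181 = 1 | 196 − 181 = 15 |

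Only women randomised in about the last five weeks (36 days at most, taking 42 weeks as the upper limit) can be undelivered at closure.

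**Step 3. Number of women affected.** The article gives no distribution of birth timing for the trial population, so this step rests on assumptions: even recruitment (3922/1096 = 3.58 per day, about 25 per week), entry uniform over 11 to 14 weeks, and normally distributed gestational age at birth, capped at 42 weeks.

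Expected undelivered = 3.58 × mean of max(0, 7 × (birth week − entry week) − 181)

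| Birth: mean (SD), weeks | Mean shortfall, days | Women undelivered | Share of 3922 |
|---|---|---|---|
| 38.5 (2.2) | 6.75 | 24 | 0.6% |
| 39.0 (1.8) | 7.87 | 28 | 0.7% |
| 39.5 (1.5) | 9.65 | 35 | 0.9% |

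Other pairings of these means and SDs give 19 to 37 women, so the order of magnitude does not depend on the choice. Among women randomised on the last day itself, about half to three quarters would be undelivered.

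**Step 4. Births before 34 weeks.** Entry at 11 weeks reaches 34 weeks after 7 × (34 − 11) = 161 days, inside the 181. None is cut off.

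**Step 5. The two calendars.** From 30 March 2022 to 1 September 2022 is 155 days, so the Study design period ends five months before the stated end of enrolment. Its October 2018 start also precedes both the July 2019 ethics approval and the September 2019 start of recruitment.

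**The case against.** The strongest reply is that no data cut-off is stated. The six months appears in a status paragraph as a rounded duration, and the article does not say that records close then or that undelivered women are censored. Hospital files and the insurance database can be read after 1 March 2023. This stands: a reader might infer that delivery, neonatal and cost data are lost, but the text does not support that. The reply does not cover data that need the woman's continued participation or later contact. Even there, the timing of the questionnaire is not given in the text, and the SPIRIT timeline figure is not shown.

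The effect is also small. Under 1% of women are affected at the central assumptions, against a planned dropout of 4.83%. The cut-off falls by calendar date on all arms, and the gestational-age endpoint given priority in the sample size concerns births before 34 weeks, which are untouched. A reader might infer a material pull toward no difference between arms; nothing in the documents quantifies one, and so few women could contribute little to it.

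Two larger figures are tempting. With a six-week postnatal window, about 150 to 180 women (3.9 to 4.5%) would have it cut short, but the article sets no such window. If the study closed on 30 March 2022 with recruitment from September 2019, only about 69% of women would have delivered, but that mixes dates from two conflicting sections. The Study design period spans 42 months, the same as 36 months of enrolment plus 6 of follow-up, so it may be the same schedule with unrevised dates. The conflict is still real and needs correcting.

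**Conclusion.** The point holds in a limited form. Six months is about three to five weeks too short to bring a last-day recruit entered at 11 weeks to 40 to 42 weeks, before any neonatal stay or postnatal assessment. Followed literally, it would leave roughly 24 to 35 of 3922 women (0.6 to 0.9%) undelivered at closure. What is then at risk is mainly their prospectively gathered RM and compliance data and the birth-experience questionnaire; the rest depends on whether records are extracted later. The omission selects later births but does not threaten the main comparison. The calendar arithmetic rests only on stated dates, while the count of women rests on assumed even recruitment, uniform entry and the birth-timing distributions shown. The contradiction between the two calendars is certain and needs no assumption. Both should be corrected; neither undermines the design.

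**What to change.** Replace the fixed six months with an end of follow-up defined per woman: delivery, discharge of mother and neonate, and completion of the planned postnatal cost and patient-reported assessments. To reach 42 weeks from entry at 11 weeks takes 217 days, a little over 7 months after the last randomisation (6 April 2023 on the stated calendar), plus whatever postnatal window the full protocol sets. State that hospital and insurance data are extracted only once that point has passed for every woman. Reconcile the dates under Study design with those under Status of the study.

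The cost is a database lock and data extraction at least 36 days later than 1 March 2023, longer with a postnatal window, and continued platform and questionnaire support for the last recruits. No additional women are needed.

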## Discussion

The PREMOM II study is the first RCT to evaluate the benefit of RM in the prenatal follow-up of pregnant women at increased risk of GHD. Our previous studies have already indicated that including RM in their care path will result in better pregnancy outcomes as well as a reduction in healthcare costs. Additionally, the stakeholders had positive views of RM. Although the results are promising, it is necessary to confirm them and to identify how RM provides these benefits. To answer these questions, we have designed PREMOM II as a multicenter RCT, in which the timing of interventions will be recorded and a PSM group will be included as a ‘placebo’ group.

Our first hypothesis is that women in the midwife-assisted RM group will have lower numbers of prenatal consultations and unplanned hospital visits compared with the PSM group and the CG. We also believe that women in the PSM group will have the greatest healthcare consumption because their vital signs are not being reviewed by a healthcare professional and no one is able to provide them with specific advice or interpretations, so these women are likely to seek clinical support. Our second hypothesis is that the gestational outcomes will be improved in the midwife-assisted RM group as a consequence of fewer inductions, a greater number of spontaneous deliveries, fewer admissions to an NICU, and fewer diagnoses of PE relative to the CG. We expect that the outcomes of the CG and the PSM group will be the same because the women in these groups are not supervised by a healthcare worker. Related to the previous hypothesis, our next hypothesis is that midwife-assisted RM will not lead to an increase in costs to the healthcare system relative to conventional prenatal care in the CG, and that healthcare costs will be greater in the PSM group than in the CG. These expectations are based on the expected prenatal follow-up and the perinatal outcomes because interventions incur costs and negative gestational outcomes are expensive, and likely to exceed the cost of RM itself. Our penultimate hypothesis is that the number of interventions will be greatest in the midwife-assisted RM group, followed by the PSM group, and the CG. This assumption considers that the timely interventions will result in fewer evolutions of GHD to PE, leading to improved perinatal outcomes in the midwife-assisted RM group. This effect is expected to be smallest in the CG. We also think that appropriate adjustment of antihypertensive medications will result in improved outcomes. Our final hypothesis is that the midwife-assisted RM group will be associated with the most positive stakeholder perceptions, followed by the PSM group. The CG is expected to report the least positive perceptions.

The ultimate goal of this project is to introduce RM into the prenatal care path for women at increased risk of developing GHD throughout Flanders. Implementing RM in every Flemish prenatal ward will ensure nearly all women in this region will have access to this healthcare strategy, improving the maternal and neonatal outcomes. From a global perspective, this RCT will provide a thorough evaluation of the benefit of incorporating RM into the prenatal follow-up of more pregnant women at increased risk of GHD. Successful results of our study will help convince the caregivers, hospital administrators, and the government to incorporate RM into routine clinical practice.

## Data Availability

The datasets used and/or analysed during the current study will be available from the corresponding author on reasonable request.

## Abbreviations

PREMOM: Pregnancy remote monitoring
RM: Remote monitoring
GHD: Gestational hypertension
PROMS: Patient-reported outcome measures
GH: Gestational hypertension
PE: Pre-eclampsia
EH: Essential hypertension
CG: Control group (conventional care)
NICU: Neonatal intensive care unit
FMF: Fetal medicine foundation tool
PSM: Patient self monitoring
IMA: Intermutualistisch agentschap
ICHOM: International consortium for health outcomes measurements
